### 3.9 G6PD status

We will assess G6PD status using the AccessBio CareStart™ RDT at the time of screening. This RDT has high sensitivity (>95%) for detecting enzyme activities  $\leq 3.6$  U/g Hb which represent ~30% of normal activity in different settings

As mentioned above, sites have the option to use the FST and if the RDT FST results are discrepant, preference will be given to the FST.

Therefore, the G6PDd group will consist of mostly hemizygous males, some homozygous females and a few heterozygous females with low G6PD enzyme activities. The RDT diagnosed “normal” group, will comprise mostly G6PD normal males and females and a G6PD heterozygous females with intermediate enzymatic activity.

The G6PD results will be used to stratify the randomisation and keep a tally of recruitment numbers by G6PD status.

### 3.10 Drug allocation and randomisation

The study has four dosing groups for the G6PDds and four dosing groups for the G6PD normals:

- AL + SLDPQ

- AL + SLDPQ placebo
- DHAPP + SLDPQ, and
- DHAPP + SLDPQ placebo.

A computer generated randomisation list will be generated for each site:

- one list for G6PDd patients and
- one list for G6PD normal patients.

The treatment allocation will be placed in a sealed opaque envelope which will be opened after a study (randomisation) number is given. The treatment allocation will describe the ACT to be given and the number of the PQ/placebo pack.

### 3.10.1 Primaquine/placebo

Owing to the low prevalence of G6PDd (~12%), the recruitment rates for the G6PDd arms will be much slower than those of the G6PD normal arms; therefore, the G6PD normals will reach their target sample size much earlier.

This will be adjusted for because there will be separate G6PDd and G6PD normal randomisation lists; this is called stratified block randomisation and is shown in Figure 1.

Figure 1. The stratified block randomisation scheme showing the final numbers to be allocated to each treatment.

[figure not shown]

### 3.10.2 Primaquine/placebo administration

PQ/placebo dosing will be based on age. There will be four blister packs labelled A, B, C and D for the four age groups (see Section 5.3). Blisters A and B will contain 2.5 mg of PQ/placebo and C and D will contain 5 and 7.5 mg of PQ/placebo, respectively.

The PQ/placebo blister packs will be labelled sequentially to match the randomisation sequence for that age dosing band and will be allocated to patients in numerical order. Therefore, each patient will have a unique drug number as well as a unique subject number.

An example of the numbering is shown below for age band A, G6PDd: A-D-001

[figure not shown]

The running number is 001 for the first patient, 002 for the second patient etc. We will discuss the drug packaging and randomisation system with Bilcare (the packaging company) and then decide on/fine tune the final labelling and randomisation scheme.

The allocation of AL or DHAPP and PQ/placebo will be organised at each site in order to minimise the chances of an error in drug allocation. Accordingly, a detailed Randomisation / Drug management guideline will be written.

### 3.10.3 Balancing recruitment numbers

Data from Kinshasa and Uganda show that children aged 6-11 months and those aged 5-11 years are relatively under represented. We will, therefore, review periodically the distribution of ages of our recruited patients from both sites combined and will aim to recruit a total of at least:

- 80 children aged 6-11m and
- 120 children aged 5-11 years.

This may require a temporary suspension of the recruitment of some age group as the trial proceeds.

### 3.10.4 Option to dose primaquine/placebo on Day 1

Data show that early vomiting within one hour can affect a significant minority of patients when treated for falciparum malaria. Children under five are most affected and rates within the under 5s are inversely related to age .

Pooled data from the World Wide Antimalarial Resistance Network show rates of early vomiting with DHAPP ranging from 3-18% on Day 0 compared to 1-9% on Day 1. Corresponding rates in AL treated children aged < 5 are from 2.3-7.3% and 0.5-6%. These data are consistent with the experience from KIMORU .

Initially, we will dose all children on Day 0 and record rates of early vomiting (indeed this is an adverse event of interest – see Section 8).

When approximately half of the patients have been recruited, we will analyse the data and consider whether we wish to dose PQ/placebo on Day 1.

### 3.10.5 Patients not completing treatment

Patients may not complete their treatment for the following reasons:

- persistent vomiting of study drugs. A patient who vomits his/her AL or DHAPP +/- PQ/placebo within one hour and also the repeat dose/s will be given rescue treatment and when better will continue follow up to D42 (see Section 6).
- the development of an adverse / serious adverse event necessitating the early stopping of study drugs; these patients will remain in the study to D42
- the PI withdraws the patient from the study before treatment is completed (see Section 4.1).

### **3.10.6 Admission to hospital**

At the KIMORU research centre in Kinshasa, study patients are routinely admitted for at least three days or longer according to their clinical course.

In Uganda, all caretakers/guardians will be invited to allow their child to be admitted to hospital for at least 48 hours for close monitoring and to receive directly observed therapy for all doses of their treatment. Children of caretakers/guardians who decline this invitation will be followed up as outpatients; this will include daily visits to the hospital so as to record clinical observations and monitor their treatment.

This decision has been taken mostly because caretakers/guardians prefer their children to be admitted.

Hb data will be continue to be sent weekly to the Data Monitoring and Ethics Committee (DMEC) by both sites.

### **3.10.7 Follow up**

After discharge from hospital, children will be reviewed as outpatients up to D42 (Appendix 1).

At each visit, the following will be done:

- clinical symptom checklist by the doctor/nurse, including vital signs
- Giemsa stained malaria blood films
- Hb & HCT or full blood count

At certain visits only, the following will be done:

- blood films for reticulocyte count
- filter paper blots for parasite genotype and qPCR for gametocytes
- venous blood samples routine biochemistry and lumefantrine blood concentration
- patients will be asked to return to the clinic at any other time if they feel unwell or develop a fever.

### **3.10.8 Blood volume**

The blood volumes per test are detailed in the schedule. The total volume of blood, including the samples for PK, is approximately 34.5 mL but allowing for spillage and/or repeat samples we seek permission for a total blood volume of 38 mL.

In patients not having intense PK sampling for primaquine, the total blood volume will be 6 mL less i.e. 29 mL but permission will be sought for 30 mL in Uganda and Kinshasa.

### **3.10.9 Duration of Study**

We expect the study to start within the first three months of 2017 and to complete recruitment and follow up within 24 months. However, we seek permission for 30 months of field time.

## **4 WITHDRAWAL & LOST TO FOLLOW UP**

### **4.1 PI withdrawal**

The PI may withdraw the patient e.g. if the study subject is poorly compliant with the study schedule or the research physicians think it is unsuitable or unsafe for the patient to continue in the study. In this scenario, follow up will cease but permission to use patient data up to the point of withdrawal will be sought.

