#### 3.3 Primary Endpoint

The primary outcome is the proportion of patients who, within the first 21 days, develop either:

- profound anaemia [Hb concentration < 4g/dL] or
- severe anaemia (Hb <5g/dL) with severity features e.g. impaired consciousness or deep breathing.

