## 4.3 Loss to follow-up

Every effort will be made to trace patients not returning to the centre for follow-up visits. Home visits will be carried out by a team member for cases who do not attend for follow-up.

A patient will be considered lost to follow up if she/he does not come for follow up and cannot be found by D42 of their schedule. Missing some follow up visits but reappearing before or on study D42 is not considered lost to follow up.

The time-window allowed for routine follow up visits:

- study day7 is +1 day
- study days 14 – 42 is -1, +2 days

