### 6.2 Oral rescue treatment

Patients will be treated with oral amodiaquine-artesunate or a different ACT according to National Guidelines if they:

- fail to either clear their *P. falciparum* parasites within the first 7 days or
- develop asymptomatic or symptomatic recurrent malaria during the follow-up

All patients who require rescue treatment will be followed-up until study Day 42.

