#### **8.4 Patient Management of Adverse Events**

All AEs will be treated as clinically indicated and concomitant treatment recorded on the Concomitant Medication CRF. If necessary, participants will be referred for specialist care.

The research team will treat and pay for minor AEs or any AE that requires hospital management that is clearly related to the study drug/s e.g. haemolysis requiring a blood transfusion.

All patients will be followed up until the AE resolved or stabilised even if this occurs past study D42. This includes patients who withdraw themselves or have been withdrawn from the study by the PI.

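### Section 4.1 stops follow-up of children the PI withdraws while 8.4 continues it, and loss to follow-up is judged at D42 although the primary endpoint closes at D21

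*Protocol*

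**What the plan says.** Section 3.3 sets the endpoint window: "The primary outcome is the proportion of patients who, within the first 21 days, develop either" profound anaemia, or severe anaemia with severity features.

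Section 4.1 lets the PI withdraw a child, for example for poor compliance, or where "research physicians think it is unsuitable or unsafe for the patient to continue in the study. In this scenario, follow up will cease". Permission is then sought only for data collected before withdrawal.

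Section 8.4 says: "All patients will be followed up until the AE resolved or stabilised even if this occurs past study D42". It adds: "This includes patients who withdraw themselves or have been withdrawn from the study by the PI".

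Section 4.3 counts a child as lost only if not found by D42: "Missing some follow up visits but reappearing before or on study D42 is not considered lost to follow up". It also provides for tracing and home visits.

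Section 11.1 adds 5% for loss to follow-up, taking 374 per group to 393, and recruits 800 G6PDd children. Section 11.2 analyses everyone who received at least one dose of ACT and of PQ/placebo.

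**The concern.** A site holding a PI-withdrawn child with a falling Hb can obey 4.1 and stop, or obey 8.4 and continue. A statistical analysis plan cannot settle this, because the choice decides whether the data exist at all.

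Section 8.4 only partly repairs 4.1. It follows an adverse event, so it does not clearly reach a child withdrawn with no ongoing event. It also does not say that Hb values obtained after withdrawal enter the primary analysis. PQ/placebo is a single dose given with the first ACT dose (5.3), so ending observation after that dose removes no PQ exposure and only loses outcome data. A judgement that continuing is unsafe may rest on a falling Hb, so the loss may depend on the outcome.

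Separately, the D42 rule in 4.3 lets a child with no Hb for much of the 21-day window be recorded as not lost, provided the child is seen again by D42. The 5% allowance and any loss figure reported under that rule would not describe completeness for the primary endpoint.

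**Working it through.** **Side by side, for a PI-withdrawn child**

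| Question | 4.1 | 8.4 |
|---|---|---|
| Does follow-up continue? | No | Yes, until the AE resolves or stabilises |
| Child with no ongoing AE | No | Not addressed |
| Data after withdrawal used? | Permission sought only for data before it | Not addressed |

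**Inputs.** Control risk 1.5%, margin 2.5 points, two-sided alpha 0.05, power 80%, 374 per group, 5% loss, 800 G6PDd children (all 11.1). Assumed: equal allocation, so 400 per arm.

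**1. The plan's own figure.** n = 2 × 0.015 × 0.985 × (1.960 + 0.842)² / 0.025² = 371.1, so 372 against the stated 374. For loss, 374 × 1.05 = 392.7, so 393 as stated. The plan's figures are reproduced to within two patients.

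**2. Expected events.** 0.015 × 400 = 6 per arm. One event moves an arm's risk by 1/400 = 0.25 points.

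**3. How few events matter.** Start from 6 v 6 and add k PQ-arm events. Wald upper limit = k/400 + 1.96 × √[p₁(1−p₁)/400 + p₀(1−p₀)/400], with p₁ = (6+k)/400 and p₀ = 6/400.

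- k = 0: 0 + 1.96 × 0.00860 = 1.7%
- k = 2: 0.0050 + 1.96 × 0.00927 = 2.3%
- k = 3: 0.0075 + 1.96 × 0.00959 = 2.6%, above the margin

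With the score interval, which takes its variance at the tested difference, k = 2 already exceeds 2.5%.

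**4. Effect on false non-inferiority.** Take true risks of 4.0% (PQ) and 1.5% (placebo), an excess equal to the margin. Multiply both by (1 − f), where f is the share of events unobserved. Sum the binomial probabilities over all pairs of counts (400 per arm) whose 95% upper limit lies below 2.5%. A missed event is taken as absent from the numerator with the child still in the denominator. That is a modelling assumption and not a rule in the protocol.

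| f, both arms (assumed) | Score | Wald |
|---|---|---|
| 0% | 2.2% | 3.3% |
| 5% | 2.8% | 4.2% |
| 10% | 3.6% | 5.4% |
| 20% | 5.9% | 8.7% |

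If 20% were missed in the PQ arm only, the figures are 9.6% (score) and 13.2% (Wald).

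**5. Does the denominator matter?** Expected counts in step 4 are 16 v 6. If 8 PQ-arm events are missed, keeping those children gives 8/400 − 6/400 = 0.50 points. Dropping them gives 8/392 − 6/400 = 0.54 points. When it is the events that are lost, the pull towards zero is nearly the same either way.

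**The case against.** Much of the protocol protects against this loss. Under 8.1 an adverse event includes an undesirable laboratory result, so a worsening Hb is itself an AE and falls under 8.4. Section 6.2 is clear on another group: "All patients who require rescue treatment will be followed-up until study Day 42". Children who do not attend are traced at home, and Hb from unscheduled visits is recorded and analysed (4.4). Hb tends to fall early (10.1), when children are admitted or, in Uganda if admission is declined, seen daily (3.10.6). All of this stands. It narrows the affected group but leaves 4.1 saying the opposite of 8.4.

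Three stronger readings are tempting, and the document does not support them.

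- *Section 3.10.5 also contradicts 4.1.* It says "the development of an adverse / serious adverse event necessitating the early stopping of study drugs; these patients will remain in the study to D42", but it lists PI withdrawal as a separate case with a cross-reference to 4.1. The two are compatible.
- *Unseen children are scored as event-free.* Section 11.2 says who is included and leaves detail to a later analysis plan. It does not say how a missing outcome is scored.
- *The event goes unseen in the children most likely to have it.* For children withdrawn as unsafe a link with Hb is plausible, but nothing shows that those who miss visits or comply poorly are more anaemic.

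The objection to the size also stands: the protocol gives no withdrawal or missed-visit rates. At 5% missed, the score-based error moves only from 2.2% to 2.8%. Recruiting 400 against 374 leaves slack too, with power about 80.9% if 5% of children are unobserved.

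**Conclusion.** The point holds as two wording faults. Sections 4.1 and 8.4 give opposite instructions on following PI-withdrawn children, and 4.1 can end primary-outcome collection for a possibly outcome-related reason. Section 4.3 measures loss against D42 when the endpoint closes at D21.

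The result is fragile because few events are expected: two or three unobserved PQ-arm events can decide it. How many would be missed is unknown. The 2.8–5.9% range rests on assumed shares of 5% to 20% in both arms, equal allocation, a 1.5% control risk and the score interval. It shows sensitivity and is not a forecast. The direction, towards non-inferiority, requires that events are lost more often than non-events. Should-fix.

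**What to change.** 1. Reconcile 4.1 with 8.4. State that PI withdrawal may end study treatment or PK sampling but does not end outcome observation. Hb, vital status and transfusion or hospital records are then still collected through D21, and to D42, and are used in the primary analysis unless the caregiver withdraws consent. Extend the data-use permission in 4.1 to match. When to withdraw a child stays with the investigators.
2. Define primary-endpoint completeness as Hb and vital status observed through the D21 visit window, and report it by arm. Keep the D42 definition for the D42 cure rate.

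An analysis counting every unobserved PQ-arm child as an event is not recommended. From 6 v 6 it fails with two (score) or three (Wald) such children, and the planned 5% loss is 0.05 × 400 = 20 per arm. It could not tell harm from ordinary attrition.

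The cost is amendment wording and, where needed, matching consent text. The visits, home tracing and AE follow-up of withdrawn children are already planned.

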## 4.2 Patient withdrawal

Study patients are considered withdrawn from the study if:

- Their caregivers/legal guardian withdraw consent for study continuation

This means no more study investigations will be done after that point.

The consent form has an option regarding the use of the child's data if he or she is withdrawn from the study by the care giver/legal guardian.

Data will not be used in the analysis unless their caregiver/legal guardian has given written consent that data can be used.

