## 11 STATISTICS

### 11.1 Sample size

The sample size is based on demonstrating non-inferiority of ACT + SLDPQ compared to ACT alone with respect to the development of profound/severe anaemia in the G6PDd group. The rate of profound/severe anaemia in AL treated uncomplicated *P. falciparum* in Kinshasa is 1.5%.

For a non-inferiority margin of 2.5%, a two sided alpha=0.05 and a power of 80%, the sample size per group is 374 patients. Allowing for a 5% loss to follow up this become 393. We will recruit 800 G6PDd patients, the majority of whom will be males.

We will also recruit 800 patients into the G6PD normal arm, for a total sample size of 1600 patients. In the G6PD normal group, we expect the male-female ratio to be close to 1 and the age distribution to be very similar to that of the G6PDd group. The majority of malaria patients will be < 5 years old.

We plan to recruit a total of 1600 patients across both sites. Local ethical approval will be sought to recruit up to 1200 patients per site in case one of the sites experiences difficulties in recruitment.

Although genetic studies have shown relative high G6PDd allele frequencies, we are mindful of the weak correlation between G6PD genotypes and enzyme activities. Therefore, we have assumed a 10% proportion of G6PD RDT diagnosed G6PDd patients (most will be male) to calculate the number of patients we will need to screen ~8500 patients to obtain 800 G6PDd patients.

For other IBDs, we expect to recruit ~596 thalassaemia heterozygotes (prevalence 37.5%), ~246 sickle cell trait (15.7%), ~103 thalassaemia homozygotes (6.6%), and 14 sickle cell disease patients (0.9%).

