## 11.2 Analyses & analysis populations

All patients who received at least one dose of ACT and PQ/placebo will be included in the analysis. All analyses will be detailed later in a prospectively written analysis plan. Below is a summary.

The main strategy for analysis of the primary end point will be assessed by chi squared or Fisher's exact test, as appropriate, calculating the 95% CIs of the risk difference to see if ACT + SLDPQ has achieved non-inferiority in the G6PDd group. Logistic regression will be used to adjust for potential confounders. Non inferiority will be assessed on the whole data set i.e. combining data from both sites using the lower end of the 95% confidence interval. Other proportional data will also be analysed by chi squared or Fisher's exact test.

Continuous data (e.g. Hb, biochemistry, parasite counts) between two groups will be analysed by the unpaired 't' test, transforming the data, as needed.

All analyses will be two sided and a p value of < 0.05 is considered statistically significant.

We will examine factors that are associated with: (i) the development of profound / severe anaemia (logistic regression), (ii) parameters of Hb recovery (multiple regression). *A priori*, we will explore the relationships between Hb profiles in the following: (i) G6PD status (defined by genotype and by enzyme activity), (ii) any IBD vs. not, (iii) age <5 vs. age ≥5y, (iv) high biomass infections, assessed by microscopy and measured HRP2 concentrations, and (v) males vs. females. For these analyses, estimates and 95% confidence intervals (CIs) will be presented but not p values.

The PK data for PQ and cPQ will be analysed by non-compartmental analysis. The following PK parameters will be estimated:

- Cmax
- Tmax
- Clearance
- Half life
- AUC
- Vd

For lumefantrine and piperaquine, drug absorption kinetics will be modelled over the first 24 hours.

The Day 7 concentrations of lumefantrine and piperaquine will be compared between PQ and placebo recipients. Depending on the lumefantrine and piperaquine data obtained, other modelled PK parameters will be determined, as the data permit.

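### Section 4.2 drops a caregiver-withdrawn child's data, including anaemia events already recorded, unless written permission exists, while section 11.2 counts every dosed child

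*Protocol*

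**What the plan says.** Section 4.2 (Patient withdrawal) covers children whose caregiver or guardian withdraws consent. On procedures it says: "This means no more study investigations will be done after that point". On data it gives two sentences: "The consent form has an option regarding the use of the child's data" if the child is withdrawn, and then "Data will not be used in the analysis unless their caregiver/legal guardian has given written consent that data can be used". Neither is limited to data from after withdrawal.

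Section 4.1 (PI withdrawal) says that follow-up stops and that "permission to use patient data up to the point of withdrawal will be sought". It does not say what happens if permission is refused or never obtained.

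Section 11.2 defines the analysis population: "All patients who received at least one dose of ACT and PQ/placebo will be included in the analysis". It makes no exception for withdrawn children.

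Section 8.4 requires adverse events to be followed until they resolve or stabilise, beyond Day 42 if necessary. It adds: "This includes patients who withdraw themselves or have been withdrawn from the study by the PI".

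Section 3.3 defines what could be lost: "The primary outcome is the proportion of patients who, within the first 21 days, develop either" profound anaemia (Hb below 4 g/dL), or severe anaemia (Hb below 5 g/dL) with severity features.

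**The concern.** The rules in 4.2 and 11.2 cannot both be followed for a child who was dosed, was then withdrawn by the caregiver, and has no written data-use permission. Since study investigations stop at withdrawal, the rule in 4.2 acts mainly on data already in hand.

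The direction of a possible bias matters here. The trial seeks to show that adding primaquine to the ACT does not raise the risk of a rare harm by more than 2.5 percentage points. Withdrawal comes after randomisation and dosing, and a falling Hb, a transfusion or a longer hospital stay could plausibly prompt it. If a primaquine-treated child with a recorded event is dropped, the event count falls and the result moves towards non-inferiority. Blinding of primaquine and placebo does not prevent this, because the haemolysis itself could prompt the withdrawal. Under 8.4 the trial might follow such an event to resolution and still leave it out of the primary analysis.

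**Working it through.** **1. The sections side by side, for a child who received at least one dose of ACT and of PQ/placebo**

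| Situation | 4.1 / 4.2 | 11.2 |
|---|---|---|
| Caregiver withdraws, permission given | data used | included |
| Caregiver withdraws, permission blank or refused | data not used | included |
| Investigator withdraws, permission obtained | data up to withdrawal used | included |
| Investigator withdraws, permission not obtained | not stated | included |

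The second row is a contradiction and the fourth is a gap. Nothing else in the protocol settles either.

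**2. The plan's own sample size**

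Inputs from section 11.1: the anaemia rate under AL "in Kinshasa is 1.5" per cent, margin 2.5%, two-sided alpha 0.05, power 80%. Assuming 1.5% in both arms:

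n = 2 × 0.015 × 0.985 × (1.960 + 0.842)² / 0.025² = 0.02955 × 7.849 / 0.000625 = 371.1, so 372 per group.

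The protocol states 374, which agrees within 2 patients. Its 5% loss allowance gives 374 × 1.05 = 393. The sample size is not in dispute.

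**3. Expected events**

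393 × 0.015 = 5.9, or about 6 per arm. One event is roughly a sixth of an arm's expected total.

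**4. Effect of removing one primaquine child with an event**

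Illustration with 393 per arm and 6 placebo events (6/393 = 1.527%; Wilson lower limit 0.702%). The removed child leaves both numerator and denominator. The event counts are chosen to lie at the margin.

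Newcombe upper limit = d + √[(u₁ − p₁)² + (p₀ − l₀)²], where u₁ is the Wilson upper limit in the primaquine arm and l₀ the Wilson lower limit in the placebo arm:

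- 8/393: p₁ = 2.036%, u₁ = 3.965%, d = 0.509%. Upper limit = 0.509 + √(1.929² + 0.825²) = 2.61%. Margin missed.
- 7/392: p₁ = 1.786%, u₁ = 3.640%, d = 0.259%. Upper limit = 0.259 + √(1.854² + 0.825²) = 2.29%. Margin met.

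Wald upper limit = d + 1.96 × SE:

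- 9/393: d = 0.763%, SE = 0.976%. Upper limit = 2.68%. Margin missed.
- 8/392: d = 0.514%, SE = 0.945%. Upper limit = 2.37%. Margin met.

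At 400 per arm (800 recruited, 1:1 assumed) the same reversals occur: Newcombe 2.56% to 2.25%, Wald 2.63% to 2.32%.

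**5. How often a trial lies that close to the margin**

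Summing binomial probabilities over all pairs of event counts, with a placebo risk of 1.5%, an assumed primaquine risk of 1.5% to 2.5%, and 393 or 400 per arm, about 7% to 12% of trials would be reversed by removing one primaquine event. That is the chance of being in the sensitive zone. It must be multiplied by the chance that a child with an event is withdrawn and lacks permission, and the protocol gives a figure for neither.

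**6. The opposite direction**

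Removing a placebo event works against primaquine. On the Wald interval, 8/393 against 6/393 gives 2.36% (met), and 8/393 against 5/392 gives 2.54% (missed).

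**The case against.** Several points on the other side have force.

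- **The consent option may precede the outcome.** Written consent comes before a study number is given. If the data-use option is completed then, the choice predates dosing, and a yes already satisfies 4.2. A reader might infer that data are lost even when nobody objects. That holds only where the option is blank, and the consent form is not available to check. The withdrawal that triggers exclusion still comes after dosing.
- **Section 4.1 states no exclusion.** A reader might infer that it deletes data in the same way as 4.2. It says only that permission will be sought. The criticism there is of an unstated outcome.
- **Section 11.2 is a summary.** It defers detail to a later analysis plan, and a specific consent restriction can be read as qualifying a general population definition. This softens the conflict. But 11.2 fixes the population without exception, and 4.2 fixes the exclusion without sparing earlier events, so the conflict is in the protocol's own text.
- **The rule may be an ethics requirement.** Section 12.1 says that the information sheets and consent forms follow local committee requirements. The sponsor may not be free to change the default alone.
- **Events are not hidden from oversight.** All SAEs are reported within 24 hours and reach the DMEC. The possible loss is from the final analysis.
- **The counts sit at the boundary.** A reader might infer from them that one withdrawn child would decide the trial, or that the result will be biased towards non-inferiority. The documents support neither, as steps 5 and 6 show.

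**Conclusion.** The point holds. Sections 4.2 and 11.2 give opposite instructions for a dosed child withdrawn by the caregiver without data-use permission, and 4.1 leaves the matching investigator-withdrawal case open. Applied as written, 4.2 can remove primary events already observed from a non-inferiority comparison on a rare harm, through a route that can depend on outcome.

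One removed primaquine event shifts the upper 95% limit by about 0.3 percentage points. That crosses the 2.5% margin only when the result already lies close to it. This rests on about 6 events per arm, on a 1.5% placebo rate taken from Kinshasa AL data, and on assumed primaquine counts of 8 or 9. The actual bias is unknown, and it could be nil if few caregivers withdraw or most give permission. The matter should be corrected because the remedy is cheap, not because harm to the result is demonstrated.

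**What to change.** 1. Reconcile 4.1, 4.2 and 11.2. Data collected up to withdrawal, in particular Hb values and primary and safety events, stay in the analysis unless the caregiver refuses in writing. Say the same for investigator withdrawals, so that 4.1 has a stated outcome.
2. State this in the information sheet and consent form for future enrolments, subject to ethics committee approval. Children already consented stay under the terms of their form.
3. Name any remaining consent-based exclusions as an exception in 11.2, and report their number by arm.
4. Add a bounding sensitivity analysis for the primary endpoint that covers excluded children in both arms: the same rule applied to each arm, plus a worst case in which primaquine exclusions count as events and placebo exclusions as non-events. Imputing events in the primaquine arm alone, without the symmetric scenario beside it, would be one-sided.

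The cost is a short protocol and consent-form amendment and one extra analysis. The sample size does not change. Version 2.0 is dated September 2018, against a planned start in early 2017 and 24 months to completion, so the consent change may reach few children. Items 3 and 4 do not depend on it and remain useful if the committees keep the present default.
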